## 8.4 Concomitant Medications

### **8.4.1 Permitted Medications**

The following medications or classes of medications will be permitted during the study when a patient is or is not receiving ARV therapy. The indication, dose, frequency, and duration of use will be recorded on a case report form.

Topical and oral antifungal agents are permitted, except for oral ketoconazole and itraconazole.

Treatment, maintenance, or chemoprophylaxis with approved agents for opportunistic infections as clinically indicated.

All antibiotics as clinically indicated (unless excluded by Section 8.4.2). Macrolide antibiotics other than clarithromycin should be used when possible. Systemic corticosteroid use for <21 days is permitted as medically indicated; chronic systemic corticosteroid use is not permitted, unless it is within physiologic replacement levels.

Regularly prescribed medications such as antipyretics, analgesics, allergy medications, antidepressants, sleep medications, oral contraceptives, megestrol acetate, pyridoxine, or any other medications are permitted as medically indicated (unless excluded in Section 8.4.2). Due to potential interactions between study medications and oral contraceptives or depoprogesterone, oral contraceptives or depoprogesterone cannot be used as the sole form of birth control.

Alternative therapies such as vitamins, acupuncture, and visualization techniques will be permitted. Herbal medications should be avoided. Subjects should report the use of these therapies; alternative therapies will be recorded but not keyed.

Although not prohibited, alcohol should be consumed with caution as it may exacerbate CNS symptoms of EFV.

Vaccinations, except any HIV vaccine, are permitted but should not be administered within 14 days before an HIV-1 RNA viral load evaluation.

### **8.4.2 Prohibited Medications**

The drugs listed in Table 8, may not be used concomitantly with the antiretroviral medication. Many of these medications are not routinely available in Uganda. During the course of the study, however, patients may gain access to some or all of these medications. With the exception of HIV vaccines, investigational agents are not allowed at any time during the study.

**Table 8**. Prohibited Concomitant Medications

| Agent by Class | Prohibited Concomitant Agents |
| --- | --- |
|  |  |
| Alternative/Complementary | St. John’s wort (*Hypericum perforatum*) |
| Analgesics | Propoxyphene |
| Antiarrhythmics | Amiodarone  Bepridil |
|  | Quinidine |
| Antihistaminics | (  Astemizole  Terfenadine |
| GI Motility | Cisapride |
| Sedative/hypnotics | Midazolam  Triazolam |
| Anti-infectives | Ketoconazole  Itraconazole |
| Other | Ergots including Dihydroergotamine, Ergonovine, Ergotamine, and Methylergonovine (Methergine™) |
|  | Thalidomide  Doxorubicin  ribavirin |

### **8.4.3 Precautionary Drugs**

Package inserts of concomitant agents should be referred to whenever a concomitant medication is initiated or a dose is changed to avoid drug interaction adverse events. Use of the agents below while on study drugs may require additional monitoring for adverse events. These precautionary medications include, but may not be limited to:

| Agent by Class | Precautionary Concomitant Medications |
| --- | --- |
|  |  |
| Analgesics | Opioids, including: |
|  | Codeine |
|  | Methadone |
|  | Morphine |
|  | Pentazocine |
| Anesthetics | Propofol |
| Antiarrhythmics | Disopyramide |
|  | Encainide |
|  | Lidocaine |
|  | Mexiletine |

| Anticonvulsants | Carbamazepine |
| --- | --- |
|  | Lamotrigine |
|  | Phenobarbital |
|  | Phenytoin |
|  | Valproic acid |
| Antihistaminics | Chlorpheniramine |
|  | Diphenhydramine |
| Anti-infectives | Clarithromycin |
|  | Dapsone |
|  | Erythromycin |
|  | Fluconazole |
|  |  |
|  |
| Beta blockers (selected agents listed, caution should be exercised for the entire class) | Atenolol  Metoprolol  Propranolol |
| Calcium channel blockers (selected agents listed, caution should be exercised for the entire class) | Diltiazem  Nefidipine  Verapamil |
| Hormonal agents | Estrogens and Progesterones |
|  | Glucocorticoids |
| Hypoglycemics | Pioglitazone |
|  | Clofibrate |
|  | Fenofibrate |
|  | Fluvastatin |
| Psychiatric medications | Bupropion |
|  | Chlorpromazine |
| Psychiatric medications | Clozapine |
|  | Fluoxetine |
|  | Nefazadone |
|  | Paroxetine |
|  | Risperidone |
|  | Venlafexine |
| Tricyclic Antidepressants (including but not limited to) | Desipramine  Imipramine  Nortriptyline |
| Sedative/Hypnotics | All benzodiazepines |
|  | Alprazolam |
|  | Clorazepate |
|  | Diazepam |
|  | Estazolam |
|  | Flurazepam |
|  | Oxazepam |
|  | Temazepam |

|  | Busprione |
| --- | --- |
|  | Zaleplon |
|  | Zolpidem |
| Other agents | Chlorzoxazone |
|  | Cimetidine |
|  | Naloxone |
|  | Promethazine |
|  | Sildenafil |
|  | T3-thyroid hormone |
|  | Warfarin |

## 8.5 Abnormal Laboratory Values

The investigator or designee will review all abnormal laboratory values (baseline or occurring during the course of a subject’s participation in the study) with regard to clinical significance and etiology (related or not related to study medication) with 24-hours of receipt of results. Laboratory abnormalities will be reported as Serious Adverse Experiences if they meet the criteria for SAE (sections 6.3.1.1).

## 8.6 Supervision of Clinical Management

Administration and monitoring for ARV efficacy and toxicity will be supervised by a U.S. trained internist with knowledge and experience in the care of HIV-infected patients and in the use of antiretroviral therapy. Before the study begins, Ugandan medical officers will have an intense initial training period on ARV therapy, directed by the study principal investigators. An on-site physician will be present for the protocol initiation to supervise the medical officers. There will be continued education for the medical officers in ARV therapy and a weekly case conference with the medical officers to review progress, medication toxicities and all protocol issues. A U.S. physician will be available for extended time periods of subsequent years of the protocol to work on site in Uganda. The study investigators will make regular site visits to assess knowledge and practice among study personnel. [name] and colleagues will oversee the ARV therapy portion of the study and will be available by email and telephone to answer all protocol related questions.

# 9.0 DATA INTEGRITY

## 9.1 Organizational Structure

The study team will be organized in three centers: a Clinical Center, a Study Coordinating Center, and a Data and Statistical Center. The Clinical Center will be located in Kampala, Uganda, at the Tuberculosis Research Clinic of Old Mulago Hospital. The main responsibilities of this Center will be screening and recruitment of study patients, provision of medical care, data collection and storage, on-site, quality assurance and control and on-site monitoring. The Study Coordinating Center will be located at CWRU in the Tuberculosis Research Unit. The main responsibilities of this center will be to coordinate study sites, protocol implementation, review of clinical events (e.g., severe adverse events, study outcomes, etc.), weekly conference calls, shipping and clearing of materials and supplies. The Data Center will be located at the San Francisco General Hospital Campus at University at California, San Francisco. We include this center because this trial will be the first antiretroviral study performed by the Uganda-CWRU Research Collaboration and represents a major new direction of research in Uganda. To ensure optimal performance of the study and safety to the participants, this Data Center, with its expertise in ARV treatment and experience in performing clinical trials of new ARV therapies, will monitor for safety and toxicity, provide quality control/assurance for data collection, and perform interim and final analyses. Prior to study implementation a manual of operations containing standard operating procedures, clinical data collection forms, protocol amendments, communications will be developed by study investigators and staff.

## 9.2 Data Collection

Clinical data will be recorded in the patient’s medical record. Copies of laboratory results will also be placed in the medical record. The medical record will represent the source document for the study. Subjects will be identified on the study forms by their study identification number and initials; full names will not be used on study forms. A dedicated data manager will provide surveillance and reporting of collected data to investigators on a routine basis.

## 9.3 Data Management

Health care providers are given in-service training by investigators about forms and study procedures before the start of the study and periodically throughout the study.

The data center will use Teleform Elite software (Cardiff Software, San Marcos California) which provides automated data entry from remote sites. Briefly, data collection forms are developed and formatted to interface with the Teleform software by study data managers. After a patient encounter, one copy of the data form is placed in the clinical chart and the other form is scanned into multi-page image files and sent to the UCSF data center. These files are compressed and stored. The data files are then read into the Teleform program, which aligns the form and records the data according to a predefined electronic template and then transferred into in a database management system.

Once in the electronic database, the data are edited and cleaned using standard programs to flag missing data and out-of-range values. Formal queries will be generated from the data center and sent to Uganda where the data managers will be responsible for responding to each query. The electronic data is backed-up on a regular basis. Complete copies of datasets will be maintained both in Uganda and at UCSF Data Center. In the U.S. Data Management Center, the data will be archived on a mainframe computer and stored in a fireproof box. This system has built-in quality assurance that begins on-site at the time of data collection and continues until the final information is validated in the final database. (Appendix VII) The hard copy data are stored in the patients’ medical records.

The specimens collected for storage are accessioned and stored either in the Joint Clinical Research Center laboratory or in the Makerere University-JHU-CWRU Research Collaboration Laboratory. The samples are entered into a database and assigned a position in one of the –70C freezers. This system allows for the ready retrieval of stored samples for later analysis. These freezers are connected to voltage stabilizers and are backed up by generators in the event of power outage.

## 9.4 Data Quality Assurance/ Quality Control

There is currently a data quality management plan in place in Uganda that has been used as part of past and ongoing IND clinical trials. This plan has been acceptable to the Division of Microbiology and Infectious Diseases and the Food and Drug Administration in the U.S. The plan assesses quality control through multiple levels of checks on data collection, entry, and storage (Appendix VII). The plan also contains regular and systematic quality assurance through the review of clinical records.

Data will be checked to insure appropriate documentation of entry criteria, accurate transfer of information from progress notes to case report form and accurate entry into the database. The goals of our quality control program will be to ensure: a) documentation of informed consent, b) completion of the case report forms, c) accurate data in the case report forms, and d) resolution of inconsistencies in the database. Results of the quality control program will be recorded on a comprehensive quality assurance form (Appendix VII).

We expect to audit all case report forms initially, and then at least 50% of forms after staff experience and accuracy is evident. Forms will be electronically transmitted within 24 hours of being seen in the clinic. Feedback will be provided to appropriate staff on a quarterly or more frequent basis, as needed.

# 10.0 STATISTICAL CONSIDERATIONS

## 10.1 Sample Size

In this randomized clinical trial we will enroll a total sample size of 350 HIV-infected TB patients into Step 2 with 175 randomized to punctuated therapy and 175 randomized to anti-TB treatment only and delayed ARV therapy. The sample size was estimated to provide a power of 80 – 90% to detect an effect size of 35% or greater for HIV disease progression. This effect size translates into an average delay of about one year before the need to start ARV therapy. The sample size will not include patients who enter Step 1 but are not eligible to progress to Step 2.

**Table 9. CD4+ cell decline before and after TB in Ugandan adults**

| Study Group | N | Rate of change in CD4+ |
| --- | --- | --- |
| Observational Cohort | 230 | One year: -83 cells/μL  Two Years: -162 cells/ μL |
| Incident TB cases | 15 | Before TB: -11.9 cells/month  After TB: -8 cells/month |
| TB Cases after treatment | 95 | Mean decline: -8.7 cells/month |

The rate of decline in CD4+ cell count has been estimated in two different groups of TB patients in Uganda (Table 9). Based on these findings, we estimate a decline of between 7 to 10 cells/month in the reference group. We therefore expect that the CD4+ count will decline at a similar rate in the TB patients receiving anti-TB treatment only and possibly delayed ARV therapy.

Effect size (ES) was used to determine power along a range of sample sizes. ES is defined as: , where λe and λr are the hazard rates for disease progression for the exposed and reference groups, respectively.73 In this trial, the exposed group will receive punctuated therapy and the reference group will receive anti-TB treatment only with possible delayed ARV therapy. The ratio of hazard rates, λe/λr, is the relative hazard and is an estimate of the relative risk for disease progression in the exposed compared with the reference group. In this analysis, we used the Cox-Mantel test to simulate power for samples sizes from 0 to 300 subjects per arm (Figure 5A and 5B) under two scenarios (see figure legend for assumptions). In one scenario, the rate of disease progression in the reference group was 50% at two years (Figure 5A), and in the other, the rate was 50% at 3 years (Figure 5B).

**Figure 5. Sample Size Calculation**

Power of designed study according to sample size per arm and effect size. Assumptions in calculations: alpha=0.05 (2 tailed), 1600 simulations, 95% confidence intervals for estimated proportions, a 3-year accrual period, and 5% dropout per year, constant hazard throughout period, and Cox Mantel-Haenszel test statistic for the comparison of two survival distributions.74 (A.) 50% disease progression by 2 years in reference group; (B.) 50% disease progression by 3 years in reference group, i.e., slower disease progression than expected. The simulations were implemented using N QueryAdvisor.75

Under the assumption that 50% of patients in the reference group will progress to CD4+ count < 250/µL within 2 years and an effect size of 35%, a power of 80% would be achieved with 125 TB patients per arm, and 90% with 175 patients per arm. Under the assumption that 50% of patients in the reference group will progress to CD4+ count < 250 within 3 years and an effect size of 35%, a power of 80% would be achieved with 175 subject per arm, and 90% with 250 subjects per arm. Based on this analysis, we chose a sample size of 175 TB patients per arm for a total of 350 TB patients. The sample size of 350 TB patients also ensures a large enough sample size to examine secondary outcomes with power of 80% or greater in each comparison.

Figure 5.

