# 3.0 study design

## 3.1 Overview

This study will be an open-label, randomized, clinical trial. The study intervention will randomize, in a 1:1 manner, 350 eligible patients with active TB and a CD4+ count greater than 350 cells/µL to receive either immediate six-month punctuated course of ARV therapy (abacavir, zidovudine, lamivudine; N = 175 patients) or anti-TB treatment only with delayed ARV therapy (N = 175 patients). Immediate, punctuated ARV treatment will be given daily for six months, concurrent with antituberculous treatment, and then interrupted until the CD4+ count drops below **250/µ**L, or a WHO stage IV AIDS defining condition develops **or a definitive diagnosis of a severe bacterial infection that meets WHO Stage 3 classification.**. Patients assigned to punctuated ARV treatment will receive a full six months of ARV treatment, regardless of when they complete anti-TB treatment. Delayed ARV treatment will be started when and if the CD4+ count drops below **250/µ**L, or a WHO stage IV AIDS defining condition develops **or a definitive diagnosis of a severe bacterial infection that meets WHO Stage 3 classification.** (Appendix II), or death, whichever occurs first. This study will have an 80% power to detect an effect size in the primary outcome of 35% or greater. This translates into an average delay of about one year before the need to start ARV therapy. Secondary outcomes will include: 1) response to antituberculous therapy as measured by sputum clearance by one and two months and rates of TB relapse; 2) safety as measured by drug toxicities and development of drug-resistance to ARVs. All patients will be offered ARV therapy when CD4+ count falls below 250/µL during the study period. The study has been designed according to the CONSORT recommendations for parallel-group randomized trials.61

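### On the plan's own inputs, 175 per arm gives about 86% and 76% power, not the stated 90% and 80%, and the one-year delay fits only the 2-year-median scenario

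*Protocol*

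**What the plan says.** Section 10.1 claims "a power of 80 – 90% to detect an effect size of 35% or greater for HIV disease progression" with 175 patients per arm. The effect size is on the hazard scale: "The ratio of hazard rates, λe/λr, is the relative hazard". The Figure 5 legend lists the assumptions as "alpha=0.05 (2 tailed), 1600 simulations", "a 3-year accrual period, and 5% dropout per year, constant hazard throughout period", and a log-rank-type test. Two reference-arm scenarios are given:

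- 50% progression by 2 years: "a power of 80% would be achieved with 125 TB patients per arm, and 90% with 175 patients per arm".
- 50% progression by 3 years, described as slower than expected: "a power of 80% would be achieved with 175 subject per arm, and 90% with 250 subjects per arm".

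On clinical meaning, section 10.1 says: "This effect size translates into an average delay of about one year before the need to start ARV therapy". The synopsis and section 3.1 repeat this, and section 3.1 states the power without a range: "This study will have an 80% power to detect an effect size in the primary outcome of 35% or greater".

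The legend gives no total duration. The synopsis sets it at 5 years with at least 2 years of follow-up per patient. That agrees with three years of recruitment (section 4.5), a five-year maximum follow-up (section 7.3.3) and the Step 3 schedule in Appendix I (two years after the last enrolment, at most 60 months).

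**The concern.** The inputs are complete enough to recompute the primary power, and the stated figures do not come back. The choice of 350 patients rests on this calculation: the lower end of the 80–90% claim is the 3-year scenario at 175 per arm. If that figure is lower, the protocol overstates the power of its primary comparison.

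The delay statement has a separate problem. With constant hazards, a fixed hazard ratio multiplies the median, so the same 35% effect is a longer absolute delay when the reference median is longer. One sentence cannot serve both scenarios. Beside a flat promise of 80% power, it could lead someone to judge a null result against a delay that the calculation does not cover in the slower scenario.

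**Working it through.** **Inputs.** Two-sided alpha 0.05; 1:1 allocation; 3-year accrual, taken as uniform; dropout 5% per year, hazard d = −ln 0.95 = 0.0513; constant hazards; total duration 5 years (synopsis). The effect-size formula is missing from the extracted text, so 35% is read as 1 − λe/λr, giving HR 0.65. Reading it as HR 1/1.35 = 0.741 would give much lower power at 175 per arm (58% and 48%), further from the stated values.

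**Formulas.** With event hazard l and s = l + d,

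P(event) = (l/s) × [1 − (exp(−2s) − exp(−5s)) / (3s)]

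Expected events D = n per arm × (P reference + P punctuated). Schoenfeld power = Φ(|ln HR| × √D / 2 − 1.96), with |ln 0.65| = 0.4308.

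**2-year median.** Reference hazard ln 2 / 2 = 0.3466, punctuated 0.65 × 0.3466 = 0.2253. P(event) = 0.642 and 0.496, sum 1.138. At 175 per arm D = 199, and 0.4308 × √199.1 / 2 = 3.04, so power = Φ(1.08) = 86.0%.

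**3-year median.** Hazards 0.2310 and 0.1502. P(event) = 0.505 and 0.372, sum 0.876. At 175 per arm D = 153, and 0.4308 × √153.3 / 2 = 2.67, so power = Φ(0.71) = 76.0%.

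| Reference median | n per arm | Events | Stated | Recomputed |
|---|---|---|---|---|
| 2 years | 125 | 142 | 80% | 72.9% |
| 2 years | 175 | 199 | 90% | 86.0% |
| 3 years | 175 | 153 | 80% | 76.0% |
| 3 years | 250 | 219 | 90% | 89.0% |

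Only the last row agrees to within 2 points. At 175 per arm, Freedman's formula gives 84.9% and 74.7%, and a direct log-rank simulation (6,000 runs per cell) gives 86.2% and 76.0%. The Monte Carlo standard error of 1,600 simulations is √(0.8 × 0.2 / 1600) = 1 point, so gaps of 4 to 7 points are not simulation noise.

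**What would be needed.** By Schoenfeld, HR 0.65 needs about 170 events for 80% power and 227 for 90%. That is about 149 and 199 per arm with the 2-year median, and about 193 and 259 with the 3-year median.

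**Attempts to recover the stated figures**, in the order of the table (stated 80, 90, 80, 90):

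- No dropout: 76.0%, 88.4%, 79.3%, 91.3%.
- Accrual at 3 per week (section 4.5), 350 / 3 / 52 = 2.24 years: 75.5%, 88.0%, 78.9%, 91.1%.
- Total duration 6 years: 78.1%, 89.9%, 82.1%, 93.1%.
- Every patient followed for 5 years: 80.3%, 91.4%, 84.6%, 94.5%.

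Each departs from a stated input, and none returns all four figures.

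**Delay.** Under constant hazards the punctuated-arm median is the reference median divided by 0.65. From 2 years: 2 / 0.65 = 3.08, a delay of 1.1 years. From 3 years: 3 / 0.65 = 4.62, a delay of 1.6 years. A one-year median delay in the 3-year scenario is HR 3/4 = 0.75; at 175 per arm that gives 161 events and 44.6% power.

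**The case against.** The best defence is that the gap is small and depends on inputs. The Figure 5 legend does not state total duration, so the recomputation joins the legend to the synopsis. At the recruitment rate projected in section 4.5, power at 175 per arm is 88% and 79%, within about 2 points of the stated round numbers. In the 3-year scenario 80% power is reached at HR 0.635, an effect size of 36.5% instead of 35%. The largest mismatch, at 125 per arm, concerns a size the trial did not choose. All of this stands and limits the weight of the point. It does not restore the figures: the legend specifies 3-year accrual, the 5-year total is consistent across the protocol, and no variant returns all four numbers.

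Three stronger readings are tempting, and the documents do not support them.

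- A reader might infer that the protocol promises adequate power for a one-year delay and delivers only 45%. It states no power for a one-year delay under a 3-year median, so the 45% contradicts nothing. It also depends on reading the average delay as a difference in medians; on exponential means it would be about 27%. In the expected 2-year scenario about one year is correct, and power for exactly one year (HR 0.667) is about 82%.
- A reader might infer that the calculation ignored staggered entry and followed everyone for 5 years. That fits the 2-year pair but gives 84.6% and 94.5% against the stated 80% and 90% in the 3-year pair. The cause is unknown.
- A reader might take the whole 3-year sentence as wrong. Its second half, 90% at 250 per arm, is essentially right.

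**Conclusion.** The stated primary power does not follow from the stated assumptions. At 175 per arm it is about 86% under the 2-year median and 76% under the 3-year median, against 90% and 80%: a shortfall of about 4 points in each. At 125 per arm it is about 73% against 80%. The one-year delay is right for the 2-year median only.

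This rests on HR 0.65 as the meaning of a 35% effect size, uniform 3-year accrual, and the 5-year total from the synopsis; with accrual at 3 per week the figures are about 88% and 79%. The primary test, alpha and sample size are unaffected, and the planned 95% confidence interval for the hazard ratio limits the harm from misreading a null result. It is a genuine correction to a stated figure, of moderate importance, and does not put the design in doubt.

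**What to change.** In the synopsis, section 3.1 and section 10.1:

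- State the total duration and minimum follow-up used in the power calculation, and the expected events at 350 patients: about 153 (3-year median) to 199 (2-year median).
- Restate power for HR 0.65 as about 76% to 86%, or about 79% to 88% if accrual follows the projected 3 per week. In section 10.1, also correct the 125-per-arm figure to about 73%.
- Say that the delay of about one year refers to the 2-year-median scenario (1.1 years), and that under the 3-year median the same hazard ratio is a 1.6-year delay.
- Optionally, note that a one-year median delay under the 3-year median (HR 0.75) has about 45% power.

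The cost is wording only, with a slightly less favourable stated power. No patients, visits or analyses are added.
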